### Exclusion criteria

Although the inclusion criteria are met, families may be excluded if their home or the school is too far from the clinic (more than 30 Kilometers). In this case the accompany to school or other outreach treatment elements are not possible. If acute crises or physical illness occur requiring inpatient treatment (e.g., suicidal crises), the rehabilitation may be interrupted for up to two weeks and then continued seamlessly. If inpatient treatment is required for a longer duration (more than 14 days), the rehabilitation project will be terminated.

Exclusion from the rehabilitation can also take place if the inclusion criteria are no longer met, e.g., if motivation for active participation in therapies can no longer be maintained. These cases will be included in the evaluation as long as the agreement is obtained.

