## Data analysis

### Quantitative data analysis

We will do statistical analysis, for example variance analysis with repeated measurement and chi-square tests to evaluate following hypotheses:
a)Main outcome: In regard of the development of school attendance and school related symptoms during treatment: The overall symptoms (SDQ) and the school related symptoms (SEQ-SS, ISV) will improve significantly from the beginning of the rehabilitation project to the end of the treatment (SDQ, ISV: T1 > T2; SEQ-SS: T1 < T2). At least 75% of the participants show a regular school attendance, defined as <10% of absenteeism in school weeks during the period T2—four weeks. The global functioning in daily life improves significantly from beginning to end of treatment (HoNOS-CA: T1 > T2).b)Follow-up assessment: In regard of the development of school attendance and school-related symptoms after the treatment: The overall symptoms and the school-related symptoms will stabilize or improve in the 6 months following the end of treatment (SDQ, ISV: T2 ≥T3, SEQ-SS: T2 ≤ T3). At least 75% of the participants achieve the proximal school goal and at least 75% of the participants show a regular school attendance, defined as <10% absenteeism during the period T3—four weeks. The global functioning in daily life is maintained or improved in the six-month following the end of treatment (HoNOS-CA: T2 ≥ T3).Data analyses will be performed with SPSS software.

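### Early exit is tied to outcome-related reasons, so a complete-case repeated-measures ANOVA, and a 75% attendance rate if taken only over those with data, risk favouring participants who stay

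*Protocol article*

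**What the plan says.** Under Exclusion criteria, the protocol article gives two routes by which rehabilitation can end early. One is prolonged hospital care: "If inpatient treatment is required for a longer duration (more than 14 days), the rehabilitation project will be terminated". The other is that the inclusion criteria cease to be met, "e.g., if motivation for active participation in therapies can no longer be maintained". The sentence that follows the second route reads: "These cases will be included in the evaluation as long as the agreement is obtained". Whether it also covers the first route is not stated.

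Under Quantitative data analysis, the methods are given as "for example variance analysis with repeated measurement and chi-square tests", and "Data analyses will be performed with SPSS software". The hypotheses are split into a main part (T1 against T2) and a follow-up part (T2 against T3) for SDQ, ISV, SEQ-SS and HoNOS-CA. The main part also sets a numerical target: "At least 75% of the participants show a regular school attendance, defined as <10% of absenteeism in school weeks". The same 75% figure is used for attendance at T3.

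Under Data collection and survey instruments, attendance is asked of students, parents and teachers, and the T2 figure covers the final four weeks of rehabilitation. Under Study design, the study has a single arm, and teachers' consent is sought during treatment because they are not always known at the start.

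**The concern.** A young person who loses motivation, or who needs a long inpatient stay, is plausibly less likely than others to be attending school regularly or to have improved. These are the participants whose later data are most at risk. Keeping them depends on agreement, and the T2 attendance window is tied to the end of a programme that they left early.

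Two separate mechanisms then matter. For the scales, a repeated-measures ANOVA in its usual form analyses only participants with every modelled visit. For attendance, a rate taken over those with data describes a selected group but would be reported against a target stated for the participants as a whole. With no control arm, there is no comparison in which such selection might partly cancel. The Discussion links continuation of the programme, and its possible extension to other clinics, to what the evaluation shows, so an inflated result would have consequences.

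**Working it through.** **Inputs from the article.** Planned N = 162 and attendance target 75%. N comes from an estimate of patient flow whose underlying count is not given, so it cannot be re-derived. The one figure that can be checked is the pilot size: 0.15 × 162 = 24.3, rounded up to 25, which agrees with the article.

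**Assumptions.** The article gives no dropout rate and no outcomes for leavers. The missing share is varied from 10% to 30%, and the proportion of missing participants who attend regularly from 0% to 75%.

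**Attendance rate.** Let m be the number missing, c = 162 − m the number observed, s the smallest whole number of successes that is at least 0.75 × c, and q the success rate among the missing. The rate in all starters is (s + q × m)/162.

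| Missing | m | Observed s/c | q = 0% | q = 25% | q = 50% | q = 75% |
|---|---|---|---|---|---|---|
| 10% | 16 | 110/146 = 75.3% | 67.9% | 70.4% | 72.8% | 75.3% |
| 20% | 32 | 98/130 = 75.4% | 60.5% | 65.4% | 70.4% | 75.3% |
| 30% | 49 | 85/113 = 75.2% | 52.5% | 60.0% | 67.6% | 75.2% |

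The 20% row in full: 98/162 = 60.5%; (98 + 8)/162 = 65.4%; (98 + 16)/162 = 70.4%; (98 + 24)/162 = 75.3%.

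**Chance of appearing to meet the target.** Suppose the true rate in all starters is 65%. With complete data, the exact binomial chance of at least 122 successes in 162 is 0.3%. With 20% missing, the rate among those observed is (0.65 − 0.20 × q)/0.80, that is 81.2%, 75.0% or 68.8% for q = 0%, 25% or 50%. The chance of at least 98 in 130 is then 96%, 51% or 6%.

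**Counting every missing participant as not regular.** Then 122 of 162 must succeed. The rate needed among those observed is 122/146 = 83.6% with 10% missing, 122/130 = 93.8% with 20% and 122/122 = 100% with 25%. With 30% missing the target is out of reach.

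**Scales.** Assume 20% are lost by T2 and 10% of the remainder by T3. Then 162 × 0.80 = 130 participants have T1 and T2, and 162 × 0.80 × 0.90 = 117 have all three visits. A three-visit ANOVA would therefore discard 13 usable T1–T2 pairs. If those who stay improve by 0.5 SD and those who leave by 0, the mean in all starters is 0.5 × (1 − missing share): 0.45, 0.40 and 0.35 SD at 10%, 20% and 30% missing.

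**The case against.** The strongest reply is that the sentence on early leavers retains them. It is not a completers-only rule, and agreement may mean no more than that the consent given at entry still stands. Some consent condition on further data is unavoidable. A reader might infer that the results will necessarily be completer results, but the article does not say that, and attendance may still come from parents or teachers. This part of the reply stands.

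It is also true that listwise deletion is nowhere stated, that ANOVA is only an example, and that a T1–T2 analysis needs no T3. A reader might infer that anyone without T3 is lost from the main comparison. That follows only if all three visits enter one model. Nor can ANOVA case deletion affect the 75% rate, which is a separate proportion.

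The missing denominator and missing-data rule would by themselves be detail that an article may leave to a fuller document. That too is right, and the point does not rest on it. It rests on what is published: exit routes related to outcome, retention subject to agreement, and a named example method that uses complete cases in its standard form.

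Two further cautions stand. Showing only 0% success among leavers would overstate the bias, so a range is given. A mixed model assumes that data are missing at random given what was observed, so it does not cure loss that depends on unseen outcomes.

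**Conclusion.** The concern holds as a risk, not as a demonstrated bias. For the scales, the named example method is a poor choice where exit is related to outcome. It loses participants with any modelled visit missing and leaves the estimate resting on those who stay.

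For attendance, the risk arises if the rate is computed only on those with data. At an assumed 20% missing, an observed 75.4% could stand for 60.5% to 70.4% of all starters when 0% to 50% of the missing attend regularly. The gap disappears if the missing attend at 75%. The direction is likely, given the stated reasons for exit, but not certain. The size depends wholly on a dropout rate and on leaver outcomes that the article does not give.

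**What to change.** 1. Analyse SDQ, ISV, SEQ-SS and HoNOS-CA with a linear mixed model for repeated measures (SPSS MIXED, time as categorical, unstructured covariance) on all available T1–T3 data. Take T2 − T1 as the main contrast and T3 − T2 as the follow-up contrast. This keeps the T1–T2 data of participants who lack only T3. It relies on missing at random and reduces the bias without removing it.

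2. Report the 75% criterion over all consented participants who started rehabilitation, with missing attendance counted as not regular. Place beside it the observed-case rate and the results under intermediate assumptions about the missing. Report how many left early and how many withdrew agreement. Counting all missing as not regular is a demanding bound, as the working shows, so it should be read together with the other rates.

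3. In the initial consent, ask for permission to obtain school-reported attendance after early termination.

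The cost is some analysis wording and one added consent sentence, with the same software. The downside is a less favourable attendance rate, possibly by several points or more: 15 points in the 20% example if no missing participant attends regularly.

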### SchuTIng-stAR interventions

The rehabilitation project is parted into three phases with four treatment levels due to school attendance can be distinguished (see Figure 2).

First, there is a preparatory phase, which begins during the ongoing hospital treatment. It includes a consultation for information about the treatment, clarification of motivation, assessment for the including criteria and specification of treatment goals. As soon as the informed consent is signed, the first participation conference will take place where the multi-professional hospital treatment team, a representative of the DRV, the family, the adolescent and the multi-professional rehabilitation treatment team meet to specify treatment goals, special needs and treatment steps. On the same day as the end of the hospital treatment, the patient is admitted to the rehabilitation project.

At this point, the second phase of treatment starts. It continues in the previous setting (inpatient or partial hospitalization unit) and lasts a maximum of four weeks. Regarding school reintegration, the adolescents are at level one, where they either continue to attend the hospital school or can start with the return to home school. Besides establishing a therapeutic relationship with the adolescents, the focus is on psychoeducational elements and the concretization of treatment goals. Interventions based on CBT, including systemic therapy and of 3rd-wave therapy interventions, are used. It is offered in individual and group settings and targets still-existing mental symptoms—as well as building self-efficacy and resilience.

There is a home visit with the nursing staff and at least one therapeutic consultation with the parents as well as occupational therapy and psychomotor treatment. This is followed by the preparation for the return to the home school and the transfer to the home environment. After at least four weeks, the child is dismissed, transferred home, and the third phase of treatment starts, which includes level two to four of school reintegration.

In level two of school reintegration, the adolescents attend home school with a reduced number of hours. They can still be accompanied to school if necessary. The weekly therapeutic sessions in individual and group settings continue.

As soon as daily school attendance is possible without accompaniment, level three of school reintegration starts, which means that school attendance is gradually increased up to standard level and any remaining special arrangements at school are dismantled.

Level four focuses on strengthening the achievements in all areas (school, family, leisure activities) and intensive relapse prevention.

There will be two more participation conferences during the rehabilitation to assess further need for support. At this point, the completely family system is looked at to identify any need for support for other family members, which may affect the child's or adolescent's school attendance in rehabilitation.

### Data collection and survey instruments

The first data collection (T1) takes place at the beginning of rehabilitation. The Strength and Difficulties Questionnaire [SDQ^2^, (37, 38)] is used for the global assessment of mental symptoms first in the full-version and then in the follow-up version at the end of the rehabilitation (T2) and six months later (T3). This questionnaire is a very often used, short, easy and economical survey to assess emotional and behavioral problems. Although there are some subscales in the German version, which shows limited reliability, the total difficulties score demonstrates satisfactory psychometric properties, as well it shows overall good criterion and construct validity (39).

In addition, the Inventory of School Refusal [ISV (40)] is used at all three times (T1-T3), which consists of several scales measuring psychological symptoms and their impact on school attendance. A child version and a parent's version are available. We chose this instrument to get more information about school related symptoms. The evaluation study of Knollmann (40) showed good internal consistency and hints for discriminating validity to distinguish between symptoms.

For the individual attitudes and expectations towards further school attendance, the adolescents fill out the Self-Efficacy Questionnaire for School Situations (SEQ-SS^3^) (41) at all three time points (T1–T3). This questionnaire measures students' beliefs about their skills to manage different school situations. The reliability demonstrates good internal consistency (Cronbach's Alpha up to 0.83) and stable test-retest values (41). The surveys can be completed in the inpatient unit or at home, using a digital version implemented with the “Unipark”-tool.

To assess the level of functioning in daily life and activities, the Health of the Nations Outcome Scale for Children and Adolescents [HoNOS-CA (42)] is used, which can be completed by therapists, nursing staff or social workers after training. It's a short and easy-to-use instrument to assess overall psychosocial functioning from a professional perspective. Although there is heterogeneity in reliability and validity (43, 44) we decided to use it in our study to assess changes in everyday functioning. At T1 and T2, this is done face-to face, at T3 it is done after a home visit or a telephone call.

To assess school attendance, information is collected from the students themselves, their parents and their teachers. We ask for the number of scheduled teaching hours (*y*) and the number of absent hours (*x*) to calculate the percentage of absenteeism (*p* = *x*/*y**100). At T1, we ask about the rate of attendance in the last three months before admission to the clinic, at T2 we ask about the rate in the last four weeks before the end of rehabilitation and at T3 we ask about the rate in the last four weeks before the measurement. In addition, we ask at T2 which proximal school level is being targeted (promotion to the next grade in the following school year or graduation) and at T3, whether it has been reached.

Further data, such as age, gender, type of school, duration of treatment, setting, and ICD-10 diagnosis are collected by interviewing the previous treatment team. Therefore, they receive the case-report form with several instructions for data collecting.

The questionnaires for the formal evaluation were designed based on key questions according to the object of research, which is to obtain information about the acceptance and active participation in the rehabilitation project. They consist of 20–27 items that can be answered on a 5-point Likert-scale. They address the organization of the project (information transfer, transparency, cooperation of the treatment team and equipment of rooms etc.), the evaluation of several elements (therapy sessions, care and education, involvement of parents/ teachers/ youth welfare services, implementation of the stepped-care approach, participation conferences) and the changes experienced in daily activities, school attendance, family life, leisure activities and peer contacts. In addition, participants are asked if they would recommend the rehabilitation project to others.

Based on the same key questions, an interview guide was developed for parents and children. The interviews are semi-structured, which means that questions can be explained or developed in more detail. To ensure the quality of the interviews, the interviewers will be trained through role-plays. The interviews will be conducted at the clinic where the rehabilitation takes place and will be done by members of the research team. The audios will be digitally recorded and then transcribed according to a fixed transcription guideline.

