### Study design

The presented study follows a mixed-methods approach: It is divided into a summative evaluation with quantitative data analysis and a formative evaluation with qualitative data analysis. The quantitative data analysis is based on a pre-post design with a six-month follow-up period. There is no control group; therefore, we have a prospective, non-randomized, non-blinded, single-arm pre-post design. Following Landes (35) and Curran (36) the study is a hybrid implementation-effectiveness study of type 1, because of both, interest and data collection in regard of effectiveness of the intervention and of information about factors that would facilitate participation for adolescents, parents and stakeholders.

Patients will be recruited from inpatient and partial hospitalization units of the LWL-University Hospital Hamm. If the clinical treatment team identifies any prognostic evidence of problems with school reintegration after hospital treatment—such as persistent preadmission absenteeism or a tendency to anxious-avoidant behavior, which can't be addressed enough by hospital treatment—they may register the patient for the rehabilitation project during ongoing clinical treatment. There are standardized criteria (see below) which has to be met.

The children or adolescents and their parents will have a thorough consultation with the responsible therapists of the rehabilitation team to receive detailed information about the rehabilitation project and the evaluation study.

There has to be a written consent from both, children and parents, to participate in the treatment and the study. The families get the information that they may be admitted to the rehabilitation project regardless of participation in the evaluation study.

Provided the adolescents and their parents give their consent, the teachers and stakeholders of other care systems involved will be informed about the study and asked for written consent in the course of treatment, as they are not always known at the beginning.

Prior to the main study, we will conduct a pilot phase with 15% of the calculated number of participants (=25 participants) to assess the feasibility and to adapt the treatment program to clinical conditions.

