### Inclusion criteria

Inclusion to the study is possible when the following criteria are met:
1.The children and adolescents to be included in the project have to be 12–18 years old and receiving treatment due to a mental health problem according to ICD-10 in an inpatient or partial hospitalization unit of the LWL-University Hospital Hamm.2.There has to be a period of at least 10% of time with school-absent behavior in the tree month before hospital treatment. This is calculated as the percentage of hours missed in relation to the number of lessons scheduled. Clinical therapists are instructed to ask this information by admission of every patient. Even if there has been no school attendance for weeks or months, patients could be included.3.The need for rehabilitation and the ability to benefit from rehabilitation has to be assessed by clinical therapists or doctors. No ICD-10 diagnoses are excluded *a priori*, but there has to be a positive prognosis regarding the success of the treatment. Therefore, criteria like medical need, physical and psychological ability to participate, basic consent about the treatment goal (reintegration into school), need for support in daily life or other limitations to participate in society are checked. This means vice versa, that a lack of basic group skills (e.g., communication skills or acceptance of group rules), acute suicidal tendencies or aggressiveness toward other patients or caregivers are exclusion criteria.If all inclusion criteria are met, the information will be passed to the rehabilitation team, in order to contact the families for further information approximately halfway through the ongoing treatment time. The inclusion will take place after the informed consent and the treatment contract have been signed. The beginning of the rehabilitation project coincides with the ending of hospital treatment. The patients remain in the same treatment unit of the LWL-University Hospital Hamm, but the rehabilitation team, which comes to the inpatient or partial hospitalization unit especially for the included patient, will replace the treatment team.

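### The SDQ changes version between T1 and T2, so any difference in scored items or reference period cannot be separated from the symptom change tested as main outcome

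*Protocol article*

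**What the plan says.** Under Data collection and survey instruments, the article introduces the SDQ as its global measure of mental symptoms and says it is used "first in the full-version and then in the follow-up version at the end of the rehabilitation (T2) and six months later (T3"). On timing, the same section states: "The first data collection (T1) takes place at the beginning of rehabilitation".

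Under Quantitative data analysis, the SDQ is part of hypothesis a), the main outcome. Symptoms "will improve significantly from the beginning of the rehabilitation project to the end of the treatment (SDQ, ISV: T1 > T2"), and the follow-up hypothesis b) is "SDQ, ISV: T2 ≥T3, SEQ-SS: T2 ≤ T3".

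Two sections fix what comes immediately before T1. Inclusion criteria: "The beginning of the rehabilitation project coincides with the ending of hospital treatment". SchuTIng-stAR interventions: "On the same day as the end of the hospital treatment, the patient is admitted to the rehabilitation project".

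Under Study design: "There is no control group; therefore, we have a prospective, non-randomized, non-blinded, single-arm pre-post design".

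The article does not say which items are scored in each SDQ version or what period each version asks about. It describes no bridging or adjustment between them. The limitations in the Discussion name the missing control group and possible changes to the intervention during the study, but not the change of SDQ version.

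**The concern.** A within-person change is interpretable only if the same quantity is measured at both ends. Here every participant moves from one version to the other at the same visit, and that visit closes the interval in which the main symptom hypothesis is tested. In a controlled trial a version difference would fall on both arms and largely cancel. In a single-arm study it has nothing to cancel against.

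The position of T1 makes the reference period matter more than usual. T1 directly follows a hospital stay whose purpose was to reduce the same symptoms. If the T1 version looks back further than the T2 version, the T1 score takes in weeks in hospital and, if the look-back exceeds the stay, weeks before admission. The T1–T2 fall would then contain improvement that had already happened when rehabilitation began. The study asks what rehabilitation adds after hospital treatment, and the Discussion says that favourable results may support continuing the programme and extending it to other clinics.

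**Working it through.** **1. Which contrasts cross the version change**

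| Contrast | SDQ version, first / second | Role in the plan |
|---|---|---|
| T1 vs T2 | full / follow-up | main outcome, T1 > T2 |
| T2 vs T3 | follow-up / follow-up | follow-up, T2 ≥ T3 |

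Only the main-outcome contrast is exposed. ISV and SEQ-SS are used at all three times with no version change stated, and none is stated for HoNOS-CA.

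**2. What the T1–T2 difference contains.** Let S1 and S2 be mean symptom levels just before T1 and T2, measured with the follow-up version. Let f be the difference due to scored items, and c the amount added at T1 by a longer look-back. Then

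observed change = (S1 + f + c) − S2 = (S1 − S2) + f + c.

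Everyone changes version at the same visit and there is no comparator, so the data give one equation for three unknowns. No analysis of these data alone can separate f and c from S1 − S2. At T2–T3 both terms cancel. If items and period are identical, f = c = 0.

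**3. When c is not zero.** Let the T1 look-back be L weeks and the hospital stay H weeks. With T1 at the end of the stay, a share min(L, H)/L of the look-back lies in hospital and max(0, L − H)/L lies before admission. The article gives neither L nor H, nor the SDQ change during the stay, so c cannot be computed. If symptoms eased in hospital and the T1 look-back is the longer one, c is positive and inflates the improvement. A version difference in the other direction would hide improvement.

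**4. How small a shift would matter.** The plan has no figure to reproduce here: it states no alpha, SDQ standard deviation or effect size, and N = 162 is a patient-flow estimate. The following is for scale only. Assumptions, none from the article: paired t-test, two-sided alpha 0.05, T1–T2 correlation r of 0.5 to 0.7, and a downward version or recall shift d of 0.1 to 0.3 SD with no true change.

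- Smallest significant standardized change: t(0.975, n − 1)/√n. For n = 162 this is 1.975/12.73 = 0.155 SD of the difference scores; for n = 81 (half the planned sample) it is 1.990/9 = 0.221.
- Shift in SD of the differences: dz = d/√(2(1 − r)). For d = 0.1 this is 0.1/√1 = 0.100 at r = 0.5 and 0.1/√0.6 = 0.129 at r = 0.7.
- Chance of a significant fall: upper tail of the noncentral t with noncentrality dz·√n. For d = 0.1 and n = 162 the noncentrality is 1.27 to 1.64.

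| Assumed shift d | 162 pairs, r = 0.5 to 0.7 | 81 pairs, r = 0.5 to 0.7 |
|---|---|---|
| 0.1 SD | 24% to 37% | 14% to 21% |
| 0.2 SD | 72% to 90% | 43% to 63% |
| 0.3 SD | 97% to 99.8% | 76% to 93% |

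With no shift the chance is 2.5%. The table shows sensitivity to a shift. It does not show that a shift exists.

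**The case against.** The strongest reply is that the article names two versions of one questionnaire and nowhere says that the scored items or the time frame differ. The follow-up version might only add questions on change. Wording of this kind is also commonly left to the full protocol. That stands as far as it goes: the existence and size of any shift are unknown.

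A reader might infer more than this: that the T1–T2 change certainly contains a version effect, that the recall periods have particular lengths, or that a given number of SDQ points would be spurious. The documents do not support any of these. They give no recall period, length of hospital stay or SDQ change in hospital, and no basis for assuming that respondents weight a long period evenly rather than answering from their recent state. That T1 is completed on the discharge day itself is also an inference. The article fixes admission to rehabilitation on that day and T1 at the beginning of rehabilitation, and lets surveys be completed on the unit or at home.

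A second reply is that any single-arm pre-post study can show improvement without a treatment effect, that the article admits this and calls the evaluation explorative, and that other measures cover the same interval. This limits the importance of the point but does not remove it. The admitted limitation concerns the missing comparator. A change of version is a separate source of error that can be avoided even without one. Nor is the choice of versions left open for another document, because the article itself fixes it.

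**Conclusion.** The concern holds in conditional form. The version change falls exactly on the SDQ main-outcome contrast. If the versions differ in scored items or reference period, the difference cannot be separated from the rehabilitation effect. If the T1 look-back is the longer one, relief from the hospital stay would be credited to the rehabilitation as well.

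The size cannot be determined from the article and is nil if items and period are identical. Under the assumptions in the working, a shift of only 0.2 SD would usually be enough for a significant result at the planned sample size, so the question is worth settling. The point is confined to SDQ T1–T2. It does not show that a positive SDQ result would be an artefact. It is a cheap improvement to a main-outcome measure and not a fault that invalidates the study.

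**What to change.** State the scored items and the reference period of each SDQ version. If both are already identical, one sentence saying so closes the point.

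Otherwise, use the same scored SDQ items with one identical reference period at T1, T2 and T3, and add the follow-up version's extra questions only at T2 and T3. For participants already assessed with a differing T1 form, report the T1–T2 SDQ change separately, list the version change among the limitations, and do not attribute that change to the rehabilitation alone.

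The practical cost is a changed instruction in the digital T1 questionnaire. The downsides are that T1 scores may be less comparable with norms for the standard form and, if the present T1 look-back is the longer one, that the expected T1–T2 change becomes smaller.
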